### Population and recruitment

Eligible participants will be community-dwelling adults aged 20 years and older, recruited from social networks, folder distribution, and digital media. The inclusion criteria are age 20 years and older, without previously diagnosed or self-reported cardiopulmonary diseases, locomotor disturbances, or other health problems that would preclude the safe performance of physical activity (e.g., electrocardiographic abnormalities during exercise test), having a smartphone, and being familiar with its use.

The exclusion criteria are average baseline level of physical activity ≥10,000 steps per day, unable to walk without the use of gait-assistive devices, recent respiratory tract infections, spirometric abnormalities, stable or unstable angina in the 4 weeks prior to examination, recent myocardial infarction, previous angioplasty or heart surgery, bradycardia or tachycardia, and refusal to participate. We set the limit of 10,000 steps per day because this is a well-known threshold for improving health [17].

### Study measurements

Participants will be assessed at baseline, and after 3 and 6 months; all assessors will be blinded to group allocation. Each assessment will include demographic and socioeconomic information, general health status, lung function, cardiorespiratory fitness, blood metabolic profile, direct and indirect levels of physical activity, blood pressure, heart rate variability, anthropometry, body composition, ideal cardiovascular health score, and muscle strength.

Assessments will be carried out in 2 days, with a 7-day interval between them. On the first day, we will assess demographic and socioeconomic information, behavior-change status for practicing physical activity, general health status, lung function, and cardiorespiratory fitness. At this point, participants will receive a blood exam form and an accelerometer, which must be used for 7 days. In the second day of assessments, participants will give the accelerometer back and will be given an assessment of their indirect level of physical activity, body composition, heart rate variability, blood pressure, anthropometry, muscle strength, and ideal cardiovascular health score.

#### Assessments

All interviews and tests will be carried out by trained staff and all equipment will be periodically checked regarding calibration.

##### Demographic and socioeconomic information

Age, sex, marital status, completed years of study, and socioeconomic classification according to a Brazilian valid questionnaire [18] will be recorded.

##### General health status

We will record information on personal and family diagnoses, medication use, and cardiovascular risk factors.

##### Behavior-change status for physical activity

To evaluate the status of behavior change we will use an adapted and validated questionnaire [19]. This questionnaire assesses the current physical activity status (practicing or not practicing) and if the person is willing to change it.

##### Lung function

Participants will perform spirometry (Quark PFT/CPET Cosmed, Pavona di Albano, Italy) following international standards [20]. We will register the forced expiratory volume in the first second (FEV_1_), forced vital capacity (FVC), and relation between the two (FEV_1_/FVC).

##### Cardiorespiratory fitness

Participants will perform a cardiopulmonary exercise testing on a treadmill (ATL, Inbrasport, Porto Alegre, Brazil) following a ramp protocol [21]. We will measure ventilatory, cardiovascular and metabolic responses, breath by breath, using a gas analyzer (Quark PFT, COSMED, Italy).

##### Blood metabolic profile

Participants will have collected a blood sample at a certified laboratory. We will register the levels of total cholesterol, HDL-cholesterol, LDL-cholesterol, fasting glucose, and triglycerides.

##### Direct and indirect levels of physical activity

The direct level of physical activity will be assessed by a triaxial accelerometer (Actigraph, Pensacola, USA), which must be used for 7 consecutive days on participants’ dominant hip. We will consider as valid data those registers of at least 4 days including at least 1 day of the weekend, for 10 h per day [22]. We will collect the number of steps per day, time in sedentary behavior, time in light activities, and time in moderate-to-vigorous activities. The accelerometer step count will be used to the exclusion criteria of ≥10,000 steps/day. The indirect level of physical activity will be calculated using the International Questionnaire of Physical Activity (IPAQ) in its long form [23].

##### Blood pressure

Participants will be comfortably sat and we will register three blood pressure measurements with a 1-min interval between them.

##### Heart rate variability

Participants will be resting in a supine position. We will register the heart rate variability for 10 min using a cardiac monitor (RS800, Polar Electro, Kempele, OY, Finland). The interval between R-waves will be analyzed using the software Polar ProTrainer 5 (Polar Electro™, OY, Kempele, Finland).

##### Anthropometry

We will measure participant height (m), body mass (kg), and abdominal circumference (cm). We will also calculate the body mass index in kg/m^2^.

##### Body composition

To assess body composition, we will use a bioelectrical impedance analyzer (310e Biodynamics, Detroit, USA), registering resistance, reactance, lean body mass (kg), and the percentage of body fat.

##### Muscle strength

We will measure muscle strength by the handgrip strength using a hydraulic hand dynamometer (Saehan, Japan), with the participant in a seated position [24]. We will register the highest value of the three measurements.

##### Ideal cardiovascular health score

The ideal cardiovascular health score will be calculated according to the American Heart Association recommendations [25].

### Data analysis

Participants’ characteristics will be presented by descriptive statistics. We will use ANOVA tests to compare the effect of interventions on the increase of physical activity levels, cardiovascular and metabolic health, lung function, and cardiorespiratory fitness among groups A + B + C and D + E + F pre- and post-intervention compared to the control group. Additionally, we will use the same test to analyze the effect of interventions on the average number of daily steps comparing the final subgroups (A to F) against the control group as well as the subgroups A + F, B + D and C + E against the control group.

To analyze the relationship between age and the response rate to each intervention, we will group responders and non-responders according to age ranges (20–30 years old, 31–40, 41–50, 51–60, 61–70, and 71 and older) and compare them in subgroups from A to F using Pearson or Spearman correlations (according to data distribution).

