**Fig. 2 Fig2:**
[figure not shown]
SPIRIT figure – protocol timeline

Assessors will be blinded to group allocation. We will randomize participants in blocks of six (two to each group) using opaque sealed envelopes and the sequence of group allocation will be computer generated.

Before randomization, all participants will watch a brief animated video about the benefits of practicing physical activity, the minimum quantity of exercise recommended to reach health benefits, and examples of daily-living situations where they can increase their levels of physical activity. They will receive a link to watch the video on the internet as many times as they want and will receive a printed booklet with the same content of the video.

Participants from groups 1 and 2 will have a commercial freely available app installed on their smartphones. This app has gamification functionalities, and it will track their daily steps. Participants will be instructed about the use and functionalities of the app, and they will be encouraged to use the smartphone close to their waist during all activities.

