### Sample size

The main objective of a SMART study relies on the feasibility of carrying out a future large-scale trial, rather than investigating the effects of the proposed set of treatments. To reach this goal, we must ensure that the number of subjects will be sufficient and balanced among all of the subgroups. According to Almirall et al. [16], a fixed probability *k* of about 80–90% should be considered so that at least *m* participants would end in non-responders’ subgroups B, C, E and F (Fig. 1). Considering a range of non-response rates in SMART studies of 35–65%, we calculated an *m* of 3 participants per subgroup as sufficient to ensure familiarity with the protocol, treatment delivery, and identification of potential problems. For a non-response rate of q = 50% at the end of the 6th week, our pilot SMART study will require 42 participants (14 per arm) [16].

After conducting this SMART pilot, we will consider the variation on the average number of steps per day to calculate the sample size of the trial, including an up to 40% loss to follow-up and a less optimistic non-response rate of 65%. To increase the feasibility of a future large-scale trial, we will calculate the sample size considering groups A + B (maintain – switch to group 2), groups A + C (maintain – switch to group 3), groups D + E (maintain – switch to group 1), groups D + F (maintain – switch to group 3), and the control group.

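### ANOVA on the pre-to-post increase does not adjust for baseline as a covariate and gives up some precision at 14 per arm

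*Protocol article*

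**What the plan says.** The Data analysis section of the Protocol article states the test: "We will use ANOVA tests to compare the effect of interventions on the increase of physical activity levels" and on the cardiovascular, metabolic, lung-function and fitness outcomes, "among groups A + B + C and D + E + F pre- and post-intervention compared to the control group". It names no covariate.

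The Study measurements section gives the schedule: "Participants will be assessed at baseline, and after 3 and 6 months". Aims and design and Follow-up both confirm that the control group is reassessed too. Each arm therefore has a baseline value for accelerometer steps and for the other outcomes. App step counts differ: they are recorded only in groups 1 and 2, so they cannot support a comparison with control.

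On size, the Sample size section says "our pilot SMART study will require 42 participants (14 per arm"). Randomisation is "in blocks of six (two to each group"), that is 1:1:1, with no stratification described.

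**The concern.** With one pre and one post value, the group-by-time test of an ANOVA is the same as a comparison of mean change scores. A change score fixes the coefficient of baseline at 1. A baseline-adjusted analysis estimates that coefficient from the data and is at least as precise in large samples.

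Two things make this worth raising here. First, with 14 per arm and no stratification described, baseline activity is balanced only by chance, and a change score over-corrects for whatever imbalance occurs. Second, the Sample size section will use the pilot's variation in daily steps to size the later trial. If that trial were planned on the same change-score test, any inefficiency would carry over.

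At stake is precision: wider intervals and larger detectable differences than the collected data allow.

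**Working it through.** **The plan's own figure.** The 42 comes from a feasibility criterion: a probability "of about 80–90% should be considered so that at least" *m* participants fall in each non-responder subgroup, with *m* "of 3 participants per subgroup as sufficient to ensure familiarity with the protocol, treatment delivery", and a non-response rate of 50%. Two subgroups per app arm need at least 2 × 3 = 6 non-responders. For n = 14, P(X ≥ 6) = 1 − 3473/16384 = 0.788, close to 80%; n = 15 is the first to reach 0.80. So 14 per arm is roughly reproduced arm by arm. It is not reproduced if both app arms must meet the criterion together (0.788² = 0.621; 16 per arm needed). None of this concerns a treatment contrast, so 14 per arm is taken as given below.

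**Inputs for the precision check.** From the document: 14 per arm, 1:1:1, ANOVA on the increase, no covariate. Assumed, because the document gives no value: ρ from 0.3 to 0.9, equal SDs at baseline and follow-up, two-sided 5% level, 80% power.

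**Variance.** In units of the follow-up variance:
- change score: 2(1−ρ)
- baseline-adjusted: 1−ρ²
- ratio: (1−ρ²)/[2(1−ρ)] = (1+ρ)/2

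**Cost of estimating the slope.** With 14 against 14 the expected inflation is 1/(28−4) = 1/24, about 4%. The net ratio is the ratio times 25/24.

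| ρ | Ratio | Net ratio | Change-score participants equal to 42 adjusted (42/ratio) |
|---|---|---|---|
| 0.3 | 0.65 | 0.68 | about 65 |
| 0.5 | 0.75 | 0.78 | 56 |
| 0.7 | 0.85 | 0.89 | about 49 |
| 0.9 | 0.95 | 0.99 | about 44 |

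The last column leaves out the slope cost.

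**Detectable difference, 14 against 14, in SD units.** This is √(variance × 2/14) × (t₀.₉₇₅ + t₀.₈₀), with 39 degrees of freedom for change and 38 for the adjusted analysis, again before the slope cost:
- ρ = 0.3: 1.29 falls to 1.04
- ρ = 0.5: 1.09 falls to 0.94
- ρ = 0.7: 0.84 falls to 0.78
- ρ = 0.8: 0.69 falls to 0.65

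**Chance imbalance.** The standard error of a baseline mean difference is √(2/14) = 0.38 SD. Given an imbalance of that size, the change-score contrast is off by (1−ρ) times it: 0.5 × 0.38 = 0.19 SD at ρ = 0.5. This is the same gain seen conditionally and must not be counted twice. At ρ = 0.5 the unadjusted excess variance is 0.19² ≈ 0.036, which equals (1.00 − 0.75) × 2/14.

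**Unequal SDs.** Let r be the baseline SD divided by the follow-up SD. The ratio becomes (1−ρ²)/(r² + 1 − 2ρr).
- r = 0.7, ρ = 0.5: 0.75/0.79 = 0.95; times 25/24, 0.99
- r = 0.8, ρ = 0.7: 0.51/0.52 = 0.98; times 25/24, 1.02

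In these two illustrations the gain is nil or slightly negative at this size.

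**The case against.** The strongest defence has three parts.

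1. **The pilot is about feasibility.** The Sample size section says so, and no treatment contrast was powered. This lowers the weight of the point but does not remove it. Aims and design makes the effect on daily steps the primary aim, Data analysis plans effect tests on many outcomes, and the Discussion expects adequate power for some key health variables.

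2. **A change score is a legitimate choice.** Under randomisation it is unbiased. This stands: the matter is efficiency, not validity.

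3. **The gain may be small.** This also stands. It fades at high ρ. For steps, excluding people at 10,000 or more per day by baseline accelerometer cuts the baseline distribution, which could make the baseline SD smaller than the follow-up SD. The document gives neither SD nor ρ, so no single figure can be claimed.

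Three stronger readings are tempting, and the document does not support them.

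- *That baseline is ignored.* It is not; it enters through the increase.
- *That participants who miss a visit will be dropped.* Data analysis states no complete-case rule, exclusion or imputation. Needing complete records is a property of one classical form of repeated-measures ANOVA, and the handling of missing visits may sit in a fuller document that is not shown.
- *That a 42-person study expects heavy loss.* The words "including an up to 40% loss to follow-up" belong to the sample size of the trial that follows the pilot, as the Abstract also makes clear. The pilot carries no attrition figure, so the two numbers cannot be combined.

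**Conclusion.** The point holds as one of efficiency. The stated ANOVA on the increase leaves baseline unadjusted as a covariate, although the value is collected in every arm. With equal SDs, adjustment cuts variance by 35% at ρ = 0.3, 25% at 0.5, 15% at 0.7 and 5% at 0.9, less about 4% for estimating the slope. The reduction is smaller, possibly nil, if the baseline SD is below the follow-up SD. Adjustment also takes out the effect of whatever chance baseline imbalance arises with 14 per arm.

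The conclusion rests on an assumed range of ρ, on the SD assumption, and on reading the ANOVA as a comparison of pre-to-post change. It says nothing about missing visits or bias from drop-out. It concerns only the arms as randomised: adjusting for baseline does not repair comparisons of subgroups formed by response.

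**What to change.** For the comparisons of A+B+C and D+E+F with control, replace ANOVA by one of:

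- ANCOVA with the participant's baseline value of the same outcome as covariate; or
- a linear mixed model of the 3- and 6-month values with arm, visit and arm × visit, and the same baseline covariate.

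Report adjusted arm-versus-control differences with 95% confidence intervals at 3 and at 6 months. For steps, use the accelerometer values, since only these exist in the control arm.

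The cost is one degree of freedom, the small slope-estimation penalty shown above, and a change of wording and analysis code. No new data are needed. The Trial status section shows recruitment still open at protocol version 4, so at that point the change could be made before analysis.

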### Aims and design

The primary aim of our study is to investigate the effect of a smartphone app combined with game elements on the level of physical activity of adults and older adults, measured by the average number of daily steps. The secondary aims are (1) to verify the effects of the intervention on cardiometabolic and cardiovascular health, lung function, and cardiorespiratory fitness; and (2) to verify the relationship between age group and the response rate.

We will conduct a Sequential Multiple Assignment Randomized Trial (SMART). This study was approved by the Ethics Committee of the Federal University of Sao Paulo (# 0499/2018) and is registered in the Brazilian Clinical Trials Registry (RBR-8xtc9c).

The SMART design has been recommended over the classical randomized controlled trial for technology-based interventions [12, 13] as it allows adaptations over time based on the participants’ response to the intervention. Despite the large potential and shown feasibility [14], the SMART design has, thus far, hardly been conducted in smartphone and gamified interventions.

The adaptive intervention protocol will last 6 months. Initially, participants will be randomized into one of three groups (group 1: app + tailored messages; group 2: app + tailored messages + gamification I; control group: physical activity counseling) (Fig. 1). Over 12 weeks, we will record the average number of steps per day for each participant from groups 1 and 2. At 6 weeks from initiation, participants will be classified into responders and non-responders according to the targeted average number of daily steps; all those considered as non-responders will be re-randomized, with the chance to participate in a third group – group 3: app + tailored messages + gamification II (Fig. 1). At the end of the 12 weeks, participants will continue using the app but will no longer receive any direct intervention from investigators. All participants, including those in the control group, will be reassessed at 3 and 6 months from baseline. The protocol timeline is shown in Fig. 2.

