## Discussion

To our knowledge, this will be the first trial with an adaptive intervention to test the effectiveness of using a smartphone app to increase the level of physical activity of adults and older adults. As stated above, the SMART design has been recommended over the classical randomized controlled trial for technology-based interventions [12, 13].

One of the major challenges of the present study will be to engage Brazilians to track their daily steps using technology. Despite the large number of smartphones in use in Brazil, whether the proposed application will be effective in this population needs more clarification. Another challenge will be the lack of security to carry out outdoors physical activities in Brazil, regardless of the neighborhood. In our recent experience, many participants from our pre-test reported not using a smartphone when practicing physical activity outdoors. We believe that creating favorable conditions for behavior change and the adoption of a healthy lifestyle will favor adherence and engagement of those involved in the study. Using the technology available on a smartphone to encourage the adoption of new ways of thinking and acting can be a new way of promoting the quality of life and well-being of the Brazilian population.

Finally, the sample size required for SMART studies is usually large and difficult to calculate. We are aware of the difficulty of involving enough people in a tight timeline. However, we are confident that we are prepared to run the protocol with sufficient statistical power, at least for some key health variables.

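### The Discussion claims adequate power for unnamed key health variables, but the pilot is sized on subgroup counts, and about 12 to 13 unranked health variables are tested against control

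*Protocol article*

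**What the plan says.** Under Aims and design, the primary aim concerns physical activity "measured by the average number of daily steps". The health domains come next: "The secondary aims are (1) to verify the effects of the intervention on cardiometabolic and cardiovascular health, lung function, and cardiorespiratory fitness".

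Data analysis then treats activity and health alike. One sentence applies ANOVA to "compare the effect of interventions on the increase of physical activity levels, cardiovascular and metabolic health, lung function, and cardiorespiratory fitness", with the comparison made "among groups A + B + C and D + E + F pre- and post-intervention compared to the control group". No variable within a health domain is singled out or ordered.

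The domains contain many measures. Under Blood metabolic profile: "We will register the levels of total cholesterol, HDL-cholesterol, LDL-cholesterol, fasting glucose, and triglycerides". Lung function records FEV1, "forced vital capacity (FVC), and relation between the two". The article also lists exercise-test responses, blood pressure, heart rate variability and an ideal cardiovascular health score.

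Sample size says that feasibility, not the study of treatment effects, is the main objective. It derives 42 participants (14 per arm) from the wish to have at least 3 people in each non-responder subgroup. The later trial is to be sized on the variation in daily steps. The Discussion nevertheless closes with "we are confident that we are prepared to run the protocol with sufficient statistical power, at least for some key health variables".

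**The concern.** The power statement in the Discussion has nothing behind it. The article names no key health variable, gives no effect size, standard deviation or power figure for any health outcome, and bases its one calculation on something else. The statement also sits badly with Sample size, which says the pilot is not mainly about effects.

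The claim matters because of the analysis it accompanies. If about a dozen unranked health variables are tested in two groups, and the key ones are left unnamed, a reader of the results cannot tell whether a variable that reaches significance was one the study was designed to detect. A nominally significant lipid or lung measure could then carry more weight than it deserves.

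**Working it through.** **1. The article's own figure.** Inputs from Sample size: m = 3 per non-responder subgroup, non-response q = 50%, probability k of about 80–90%, 14 per arm. Each app arm feeds two non-responder subgroups, so it needs at least 2 × 3 = 6 non-responders:

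P(X ≥ 6), X ~ Binomial(14, 0.5) = 1 − (1 + 14 + 91 + 364 + 1001 + 2002)/16384 = 1 − 3473/16384 = 0.788.

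This is close to the lower end of k, so 14 per arm is reproduced approximately, reading k per arm. No outcome, effect size or variance enters the calculation.

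**2. Power that 14 per arm gives.** Each pooled app group is one original arm, so the comparison with control is 14 against 14. Assumption: two-sided 5% (the article states no alpha). With standardised difference d, the noncentrality is d√(n/2) = d√7 = 2.646d, on 26 degrees of freedom with critical t = 2.056.

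- d = 0.5: noncentrality 1.32, power 25%.
- d = 0.8: noncentrality 2.12, power 53%.
- 80% power: d = 1.10.

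The normal approximation is slightly kinder: 26%, 56%, and d = (1.960 + 0.842) × √(2/14) = 1.06. The one effect size cited in the Background, 0.54, concerns physical activity rather than a health outcome; at that size, power would be 28%.

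**3. Number of health variables.** 5 blood + 3 lung function + at least 1 exercise-test measure + 2 blood pressure (systolic and diastolic, an assumption) + at least 1 heart rate variability + 1 cardiovascular health score = 13, or 12 if blood pressure counts once. Anthropometry, body composition and grip strength are left out. With two app groups, that is 13 × 2 = 26 comparisons (24 with 12 variables).

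**4. False positives when nothing works.** Assumption: each comparison is tested at two-sided 5% without adjustment. For independent tests:

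- 26 tests, either direction: 1 − 0.95^26 = 73.6%.
- 26 tests, direction of benefit only: 1 − 0.975^26 = 48.2%.

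The tests are not independent, because the two app groups share the control group and health measures are correlated. Simulating null trials with three arms of 14, 13 equally correlated outcomes, one follow-up and pooled-variance t tests (40,000 trials per row) gives:

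| Outcome correlation | Any false positive, ungated | False benefit, ungated | Any, gated by three-group ANOVA | False benefit, gated |
|---|---|---|---|---|
| 0 | 71% | 45% | 43% | 24% |
| 0.3 | 63% | 35% | 38% | 20% |
| 0.5 | 53% | 27% | 31% | 16% |
| 0.8 | 33% | 17% | 18% | 9% |

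With 12 variables, the ungated rates are 68%, 61%, 51% and 32% for any false positive, and 43%, 33%, 26% and 16% for a false benefit.

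**The case against.** The strongest reply is that this is a condensed article. Alpha, multiplicity rules and the ordering of secondary outcomes usually belong in an analysis plan, which is not shown. That stands: silence on adjustment is not a fault here, and a reader who infers that every test is run at full alpha goes beyond the text. An unseen plan would not correct the Discussion sentence, though, because that is something the article positively asserts.

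Nor is there a complete lack of hierarchy. Daily steps are primary and the health domains are a secondary aim. Only an order within the health family is absent.

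A reader might also infer that a chance health benefit is more likely than not. The documents do not support this. The rates above 50% count apparent harms as well as benefits. In the direction of benefit alone, even 26 independent tests stay below one half (48.2%); it takes 28 (1 − 0.975^28 = 50.8%). Testing both follow-up visits separately would raise the false-benefit rate for 13 outcomes to about 65%, 51% and 41% at outcome correlations 0, 0.3 and 0.5 (assuming correlation 0.6 between visits). But Data analysis speaks only of pre- and post-intervention and does not specify a test at each visit.

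The wording on ANOVA can also be read as an overall three-group test that gates the comparisons with control. On that reading all rates fall, and none in the table exceeds 43%.

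Finally, the Discussion may have the later, larger trial in mind. That does not rescue the claim: no size is given for that trial, and it is to be sized on steps. That the authors would relabel a chance finding as key is conjecture, and the point does not depend on it.

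**Conclusion.** The point holds in this form: the article claims sufficient power for health variables it does not name, and its only sample size calculation does not bear on any of them. At 14 per arm and an assumed two-sided 5%, power is about 25% at d = 0.5 and 53% at d = 0.8, and only differences of about 1.1 standard deviations reach 80%.

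The unranked testing of about 12 to 13 health variables in two groups makes the claim more consequential. If the tests are ungated and unadjusted at 5%, at least one false positive in either direction occurs in about 53% to 71% of null trials with 13 outcomes at correlations of 0.5 to 0 (about one third at 0.8). A false benefit occurs in about 27% to 45% (16% to 17% at 0.8). These rates rest on an alpha and a testing rule that the article does not state, and they are upper figures if an ANOVA gates the comparisons. The power claim is the firm part; the error rates show what could follow from it.

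**What to change.** In the Discussion, delete the power claim or restate it to say that the pilot is not powered for any health variable.

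In Data analysis, choose one of two statements:

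- All health outcomes other than daily steps are exploratory and are reported as between-group differences with 95% confidence intervals, without claims of effect.
- One named health outcome is a confirmatory secondary outcome, fixed now and tested only after the primary step comparison succeeds; the rest are exploratory as above.

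If an analysis plan already contains such a rule, a one-line reference to it is enough for Data analysis, but the Discussion sentence still needs to change.

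The cost is wording only: no visit, measurement or participant is affected. The downside is that a single nominally significant health variable could not be claimed as a proven effect.
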